## Abstract

**Background:**

The National Institute for Health and Care Excellence (NICE) recommends that cognitive behaviour therapy (CBT) is offered to all patients with a psychosis diagnosis. However, only a minority of psychosis patients in England and Wales are offered CBT. This is attributable, in part, to the resource-intensive nature of CBT. One response to this problem has been the development of CBT in brief formats that are targeted at a single symptom and are deliverable by briefly trained therapists. We have developed Guided self-help CBT (the GiVE intervention) as a brief form of CBT for distressing voices and reported evidence for the feasibility of a randomised controlled trial (RCT) when the intervention was delivered by briefly trained therapists (assistant psychologists). This study will investigate the clinical and cost-effectiveness of the GiVE intervention when delivered by assistant psychologists following a brief training.

**Methods:**

This study is a pragmatic, two-arm, parallel group, superiority RCT comparing the GiVE intervention (delivered by assistant psychologists) and treatment as usual to treatment as usual alone, recruiting across three sites, using 1:1 allocation and blind post-treatment and follow-up assessments. A nested qualitative study will develop a model for implementation.

**Discussion:**

If the GiVE intervention is found to be effective when delivered by assistant psychologists, this intervention could significantly contribute to increasing access to evidence-based psychological interventions for psychosis patients. Furthermore, implementation across secondary care services within the UK’s National Health Service may pave the way for other symptom-specific and less resource-intensive CBT-informed interventions for psychosis patients to be developed and evaluated.

**Trial registration:**

Current Controlled Trials ISRCTN registration number: 12748453. Registered on 28 September 2022.

## Introduction

### Background and rationale {6a}

Approximately 300,000 people in England and Wales have a diagnosis of psychosis [1]. The symptoms of psychosis such as paranoid delusions and hearing voices (hereafter referred to as distressing voices) cause significant distress and disability and contribute to an increased risk of physical health problems and early mortality [2], and suicide rates up to twelve times greater than the general population [3]. The overall annual societal cost of psychosis in England has been estimated at £11.8 billion [4].

Cognitive behaviour therapy for psychosis (CBTp) has robust evidence for clinical [5] and cost-effectiveness [6] and is recommended by the National Institute for Health and Care Excellence (NICE) to promote the recovery of psychosis patients [6]. However, implementation in the UK is extremely poor, [7] with only 26% of psychosis patients being offered CBTp [1]. One reason for this lack of access is limited resources, [8] as CBTp is resource-intensive in relation to its duration (minimum of 16 sessions recommended by NICE) and delivery (by highly trained therapists—who are trained over a 2–3-year period).

NICE recommend research into two issues that could potentially reduce the resources required to deliver CBTp to psychosis patients [6]. Firstly, the duration of CBTp—how many sessions are required to generate sufficient benefit (research recommendation 9.4.11.1)? Our meta-analysis of 10 controlled studies indicated that CBTp delivered over less than the recommended 16 sessions is effective in reducing psychosis symptoms when delivered by highly trained therapists [9]. This focus upon brief forms of CBTp has recently been taken forward through the development of single-symptom therapies [10] which target only one specific psychotic symptom, with some promising early results [11]. Secondly, the ability of “briefly trained” practitioners to deliver CBTp—can CBTp be delivered by a more cost-effective alternative workforce (i.e., not highly trained therapists) (research recommendation 9.4.11.2)? Evidence suggests that frontline practitioners with case management responsibilities can struggle to fulfil this role as outcomes from trials have been inconclusive [12, 13] and there are competing demands upon their time [14, 15]. Psychology graduates, however, are well-positioned to undertake such a role [14–16] as there is a large number of psychology graduates in the UK; their degree provides them with training in psychological models of emotion and behaviour; they can be readily employed in assistant psychologist (AP) roles at lower cost than highly trained therapists; and they do not have case management responsibilities.

We have packaged CBTp in a brief and structured form that is targeted at the specific psychotic symptom of distressing voices. We collaborated with people with lived experience of psychosis and/or distressing voices to turn our self-help CBT book (Overcoming Distressing Voices [17]) into a workbook (An Introduction to Self-help for Distressing Voices [18]) and created the Guided self-help CBT intervention for distressing VoicEs (the GiVE intervention). We initially evaluated the GiVE intervention when delivered by highly trained therapists, as this allowed the evaluation to focus exclusively upon CBT packaged in this form, rather than any interaction between the GiVE intervention and delivery by briefly trained therapists. The findings from a pilot randomised controlled trial (RCT) of GiVE compared to usual care (*N* = 28) were encouraging with high levels of retention, and a very large between-group effect for the predetermined primary outcome of negative voice-impact (Cohen’s *d* = 1.78) [19]. Our next step was to evaluate the GiVE intervention when delivered by a cost-effective and widely available workforce of APs. We conducted a three-arm, multi-site feasibility RCT comparing the GiVE intervention (delivered by APs over 8 sessions) to a Supportive Counselling intervention (delivered by the same APs over 8 sessions—the active control intervention) and to treatment-as-usual (TAU). The progression criteria were met and suggested that clinicians were willing to refer psychosis patients to the trial, that patients could be retained within the trial at post-treatment and that the APs could adhere to therapy and supervision protocols. A signal of efficacy favouring the GiVE intervention in comparison to both the Supportive Counselling intervention (Cohen’s *d* = 0.77) and TAU (Cohen’s *d* = 0.49) was evident at post-treatment (16 weeks after randomisation) for the candidate primary outcome (voice-related distress) [20]. The lessons learnt from the feasibility RCT have informed the design of the current study.

If the GiVE intervention is found to be clinically and cost-effective in the current study when delivered by APs, it could substantially increase the number of psychosis patients that are able to access and engage with the principles of CBT, which will generate benefits for psychosis patients and the NHS.

### Objectives {7}

The long-term aim of this research is to increase access to CBTp for psychosis patients; this will be achieved by evaluating the clinical and cost-effectiveness of a brief and targeted CBT-informed intervention that can be delivered by a less costly and widely available workforce of APs following a brief training in the delivery of the intervention and ongoing supervision. CBT-informed interventions offered to psychosis patients in less resource-intensive forms as part of an evidence-based intervention pathway will generate benefits for (1) individual patients (reduced distress and enhanced recovery); (2) service-level patient benefit (increased access to evidence-based psychological therapies); and (3) economic benefits to the NHS (in terms of the reduced use of high-cost mental health services).

The proposed study will evaluate the following hypothesis: In comparison to usual care, is the GiVE intervention effective at treating distressing voices when delivered to psychosis patients by briefly trained APs?

### Trial design {8}

This study is a pragmatic, two-arm, parallel group, superiority RCT comparing the GiVE intervention (delivered by APs) in addition to treatment as usual to treatment as usual alone, recruiting across three sites, using 1:1 allocation and blind post-treatment and follow-up assessments.

## Methods: participants, interventions and outcomes

### Study setting {9}

The study will be conducted within Secondary Care Adult Mental Health Services in three large NHS Mental Health Trusts in Sussex (rural), Greater Manchester (urban) and North-East England (rural). The study intervention will be delivered by six therapists (two per site) who will each have their own caseload of 10–11 participants (across the duration of the intervention delivery period).

### Eligibility criteria {10}

In contact with Secondary Care Mental Health Services (under the care of a mental health team within one of the recruiting Trusts)Have a clinician-reported diagnosis of psychosis (including schizophrenia spectrum disorder [ICD10 F20–29] or affective disorder with psychotic symptoms [ICD-10 F30–39, subcategories with psychotic symptoms])Aged 18 or overWilling to provide informed consentExperiencing current voice hearing; this will be operationalised by participants having a score of at least 1 on item 1 (‘Frequently’) on the Psychotic Symptoms Rating Scale—Auditory Hallucinations Scale (PSYRATS-AH [21]) at the time of consent—indicating that the participant has experienced at least one episode of voice hearing in the past weekScoring 3 or 4 (rated on a 0–4 scale) on either the intensity of distress item or the amount of distress item on PSYRATS-AH [21] at the time of consent.

#### Exclusion criteria

Established organic cause for distressing voicesPrimary diagnosis of substance misuseCurrently detained in hospital under a section of the Mental Health ActHaving completed a full course (minimum of 16 h) of CBTp for psychotic symptoms during the past yearImmediate and serious risk to self or others (assessed at the point of referral/eligibility review)

If inclusion and exclusion criteria are met, every effort will be made to include and support the participation of patients who experience challenges with respect to language and literacy. This will include the use of the translation and literacy services that are routinely available within the clinical services of the host sites and the informal support that is available within the participant’s network. The recruitment resources will be available in Easy Read versions.

### Who will take informed consent? {26a}

Consent to take part in this study will be informed. All participants will be given the participant information sheet (PIS) at least 24 h before meeting with a research assistant (RA) to give consent. Furthermore, participants will have the opportunity to ask questions about the research study before providing consent. The combination of the PIS and the opportunity to ask questions of the RA will ensure that any consent given will be fully informed.

### Additional consent provisions for collection and use of participant data and biological specimens {26b}

On the consent form, participants will be informed that their data will be retained should they choose to withdraw from the trial. Participants will also be asked for permission for the research team to share relevant data with people from the NHS Trusts taking part in the research or from regulatory authorities, where relevant. This trial does not involve collecting biological specimens for storage.

## Interventions

### Explanation for the choice of comparators {6b}

A two-arm RCT was chosen to enable (1) any effect of GiVE to be differentiated from the impact of standard care (available within TAU); and (2) an evaluation of the cost-effectiveness of GiVE—generated by a comparison to the treatments that are usually offered to patients (available within TAU).

### Intervention description {11a}

#### Guided self-help intervention for voices (GiVE)

The intervention is described in our published workbook [18] and will consist of 10 one-hour sessions of the GiVE intervention over a 16-week period, delivered by APs in NHS clinics, participants’ own homes or other community locations as preferred and appropriate. Where participants express a preference for the intervention to be delivered remotely (by videocall or phone), this preference will be honoured. GiVE is a psychological intervention that targets the mechanisms that have been empirically found to maintain voice-related distress—negative beliefs about voices, [22, 23] negative beliefs about self [24, 25] and negative relating [26, 27]. After the introductory sessions (including a focus upon coping), the intervention will cover three core modules: (1) beliefs about the self, (2) beliefs about voices and (3) relationships. Modules (1) and (2) draw upon psychoeducation and cognitive behavioural strategies to help participants to re-evaluate the accuracy of their negative or unhelpful beliefs related to the self and voices. Module (3) additionally involves work on how to relate to others and voices more assertively.

A participant will have received sufficient ‘exposure’ to the intervention if they have attended a minimum of 6 of the 10 sessions.

Participants will be provided with a copy of the workbook [18] and companion self-help book [17] and will be ‘guided’ through the structured content of the workbook by an AP—with encouragement to complete between-session exercises in the workbook and to read relevant chapters of the self-help book. Participants will also have the opportunity to access the ‘CHOICES’ mobile phone application. The ‘CHOICES’ app was developed by Sussex Partnership NHS Foundation Trust to support the learning of patients within its clinical services. The app has been revised for use in this trial and aims to support the continued use of strategies that have been learnt through the GiVE intervention. If participants have a smart/ iPhone and are familiar with accessing mobile phone apps, the AP will provide them with a guide to access the CHOICES app. The research team will have no access to the data entered by participants into the app.

Consistent with the previous recommendations from Experts-by-Experience (EBEs), we will recruit APs who have some experience of working as an AP with patients with complex needs. The APs will receive a brief 3-day training in the delivery of the GiVE intervention facilitated by the Chief Investigator. The training will include 1 introductory day (covering the experience of distressing voices and CBT principles) and 2 days on the GiVE intervention (covering the content of the workbook) and will be delivered to all APs at the same time.

Two APs will offer the GiVE intervention at each site. The APs will be offered weekly clinical supervision by the Site Leads, including both 1:1 supervision at site and group supervision at both site and remotely across sites. Participants in the GiVE arm will continue to receive treatment as usual (described below) throughout their participation in the study.

#### Treatment-as-usual

Treatment as usual (TAU) will be delivered according to national and local service protocols and guidelines and mainly consist of antipsychotic medication and support and monitoring from the local clinical team, with individual and family psychological therapies offered occasionally.

### Criteria for discontinuing or modifying allocated interventions {11b}

The intervention may be discontinued if the participant requests this or if the AP judges, in consultation with the wider supervisory team, that the intervention is associated with a significant worsening of mental health. In this case, an adverse event form would also be completed. It will be made clear to each participant that, should they find any aspect of the research distressing, including the intervention, and/or no longer wish to continue, they will be able to withdraw without this impacting on their usual clinical care in any way.

### Strategies to improve adherence to interventions {11c}

Therapeutic drift will be minimised by the structure and detail of the workbook and close supervision of the APs by the Site Leads. Adherence to the workbook will be assessed through APs completing a session checklist at the conclusion of each session. All therapy sessions will be audio-recorded (with the participant’s consent—which will be verbally re-affirmed at the beginning of each therapy session) and a random 10% sample rated for adherence and competence by an independent CBT expert. These recordings will be rated for adherence using the session checklist. In addition to providing an independent assessment of the AP’s delivery of the session content, cross-referencing of the self-report and independently rated checklists will offer insights about the ability of APs to monitor their own performance. Session recordings will also be rated for competence using a version of the Cognitive Therapy Scale-Revised (CTS-R) [28] that has been adapted for use within the training of ‘lower-intensity’ therapists within the NHS Talking Therapies services within Sussex.

### Relevant concomitant care permitted or prohibited during the trial {11d}

Participants in both arms of the trial will be encouraged to engage in and continue with existing treatments. Our methodological approach will be to carefully monitor and capture the service contacts received across a range of services in both arms of the trial using an adapted version of the Client Service Receipt Inventory (CSRI) [29].

### Provisions for post-trial care {30}

There is no provision for post-trial care in the study, and participants will remain under the care of their usual mental health services.

### Outcomes {12}

#### Screening measures

Psychotic Symptoms Rating Scale—Auditory Hallucinations Scale (PSYRATS-AH) [21]This 11-item observer rating scale assesses the characteristics of voices across four scales—distress, attribution, loudness and frequencyThe measure is used at screening to assess the presence of voice hearing experiences and associated levels of distress

#### Demographic measures

2.Information About You survey

#### Clinical measures

3.Primary outcome: Psychotic Symptoms Rating Scale – Auditory Hallucinations (PSYRATS-AH) [21]◦ The 5-item ‘distress’ subscale measures the impact that voices have on the individual and will be the primary outcome◦ The subscale is an observer rated measure that consists of 5 items◦ This measure is included as the study intervention aims to reduce the distress associated with hearing voices◦ The primary endpoint will be 16 weeks post-randomisation.

4.Secondary (clinical) outcome: Psychotic Symptoms Rating Scale—Auditory Hallucinations (PSYRATS-AH) [21]◦ The subscales of attribution (2 items), loudness (1 item) and frequency (3 items) measure the characteristics of voices beyond distress.◦ These characteristics are not targeted by the intervention but can change during therapy.

5.Secondary (clinical) outcome: The Hospital Anxiety and Depression Scale (HADS) [30]◦ Any changes in distress related to voice hearing experience may reflect a more global reduction in emotional distress—therefore this measure will allow such changes to be captured.

6.Secondary (clinical) outcome: CHoice of Outcome In Cbt for psychosEs (CHOICE) [31]◦ The CHOICE was developed in partnership with patients to measure recovery and therefore reflects the outcomes that are important to them◦ The 12-item short form of this measure will be used.

7.Secondary (mechanism) outcome: The Brief Core Schema Scale (BCSS)—self scale [32]◦ One of the modules within the GiVE intervention focuses on beliefs about the self. This 12-item measure assesses the degree of positive and negative beliefs the person has about themselves

8.Secondary (mechanism) outcome: Approve – Voices [33]One of the modules within the GiVE intervention focusses on relationships. This 15-item measure assesses the styles of relating to voices across three subscales—assertive, aggressive and passive.

9.Secondary (mechanism) outcome: Approve—Social [33]One of the modules within the GiVE intervention focusses on relationships. This 15-item measure assesses the styles of relating to other people across three subscales—assertive, aggressive and passive.

10.Secondary (mechanism) outcome: Beliefs about voices questionnaire—revised (BAVQ-R) [34]◦ One of the modules within GiVE targets beliefs about voices. This measure can assess the degree to which these beliefs are positive or negative, and may be changing during therapy◦ The 14-item version of this measure will be used to capture ‘persecutory beliefs’ and ‘benevolent beliefs’.

11.Secondary (clinical) outcome: Revised Green Paranoid Thoughts Scale (R-GPTS) [35]◦ Interventions that target one specific symptom of psychosis may have an impact upon other psychosis symptoms. This 18-item measure will capture any impact upon paranoid delusions.

#### Health economic measures

12.Client Service Receipt Inventory (CSRI-UK) [29]◦ This instrument will be used to collect information on service utilisation, income, accommodation and other cost-related variables◦ Its primary purpose is to allow resource-use patterns to be described and support costs to be estimated.

13.EQ-5D-5L [36]◦ This standardised instrument will be used as a measure of health-related quality of life relevant to a wide range of health conditions and treatments◦ The descriptive system comprises five dimensions: mobility, self-care, usual activities, pain/discomfort and anxiety/depression. Each dimension has 5 levels: no problems, slight problems, moderate problems, severe problems and extreme problems.

14.SF-12 v2 [37]◦ This generic health survey captures information about functional health and well-being from the patient’s point of view.◦ It consists of 12 questions that measure 8 health-related domains around physical and mental health. The physical health-related domain covers General Health, Physical Functioning, Role-Physical and Body Pain while the mental health-related domain covers Vitality, Social Functioning, Role Emotional and Mental Health.

### Participant timeline {13}

Figure 1 illustrates the trial/recruitment flowchart.

**Fig. 1 Fig1:**
[figure not shown]
Trial/recruitment flowchart

### Sample size {14}

Under simple randomisation, to detect a medium effect size of Cohen’s *d* = 0.5 with 90% power for 5% significance with one baseline measure and two follow-up measures, with correlation between these of 0.6 [38], 37 participants per arm are required. The adjusted standard deviation obtained from this calculation is 0.663 (step 1).

To estimate the power for a design with clustering in one arm only, we used the following parameters: 6 therapists each with a caseload of 8 participants completing follow-up assessments, an intracluster correlation coefficient (ICC) of 0.05 [39], an equally sized group (for maximum efficiency) of 6 × 8 = 48 unclustered participants for the treatment as usual arm (ICC = 0), a 5% significance level, adjusted variance from Step 1, i.e. 0.663, a medium effect size of Cohen’s *d* = 0.5. This resulted in an estimated power of 88%.

We assume 26% attrition so the sample size to be recruited is 96/(1 − 0.26) = 130 participants, i.e. 65 per group implying a caseload of between 10 and 11 participants per therapist over the course of the intervention.

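### The stated 88% power is for the average of the 16- and 28-week effects; for the declared 16-week primary endpoint the same inputs give about 75%

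*Protocol article*

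**What the plan says.** All references are to the protocol article.

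- **Sample size {14}, step 1.** The target is d = 0.5 "with 90% power for 5% significance", and the step continues: "with one baseline measure and two follow-up measures, with correlation between these of 0.6 [38], 37 participants per arm are required". The adjusted standard deviation from this step is given as 0.663.
- **Sample size {14}, step 2.** Clustering is in the GiVE arm only: 6 therapists with 8 completers each, ICC 0.05, against 48 unclustered controls. The step takes "adjusted variance from Step 1, i.e. 0.663" and d = 0.5, and reports a power of 88%. Recruitment is then inflated for 26% attrition to 130.
- **Outcomes {12}, Clinical measures.** For PSYRATS-AH Distress: "The primary endpoint will be 16 weeks post-randomisation". The section on the primary clinical measure under Data collection repeats the 16-week time point.
- **Statistical methods {20a}.** The primary model has fixed effects for baseline, site and allocation, and random effects for therapist/control participant and for repeated observations. The difference between arms, its confidence interval and its p value are to be reported for each time point separately. A small-sample correction is planned, with Satterthwaite as the example.

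**The concern.** The two parts of the protocol refer to different treatment effects. Averaging two follow-ups removes part of the within-person noise, so an averaged effect is estimated more precisely than the effect at either visit. The sample size takes credit for that averaging, while the primary endpoint is a single visit. No section names the 16/28-week average as the primary effect.

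What is at stake is how the result is read. A non-significant 16-week difference would be interpreted as coming from a trial with a 12% chance of missing d = 0.5, when that chance is nearer one in four. The planning effect leaves little slack: Background {6a} reports d = 0.49 against usual treatment at 16 weeks in the feasibility trial.

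A second, smaller slip is that step 1 calls 0.663 a standard deviation and step 2 calls it a variance.

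**Working it through.** **Inputs (all from Sample size {14}).** d = 0.5 on an unadjusted SD of 1; correlation ρ = 0.6; one baseline; two follow-ups; 5% significance, taken as two-sided because that reproduces the printed figures; 6 therapists × 8 completers = 48 in the GiVE arm; 48 controls; ICC 0.05 in the GiVE arm and 0 in controls.

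**Step 1, reproducing the plan.** For the mean of r follow-ups adjusted for one baseline, the variance factor is

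v = (1 + (r − 1)ρ)/r − ρ².

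- r = 2: v = 1.6/2 − 0.36 = 0.44, SD = 0.663. Then n = 2 × (1.960 + 1.282)² × 0.44/0.25 = 36.99, so 37 per arm. Both printed figures are reproduced.
- r = 1 (16 weeks only): v = 1 − 0.36 = 0.64, SD = 0.80. Then n = 2 × (1.960 + 1.282)² × 0.64/0.25 = 53.8, so 54 per arm before any allowance for clustering.

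**Step 2, reproducing the plan.** With clustering in one arm,

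SE² = v × (1 + 7 × 0.05)/48 + v/48,

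and the Satterthwaite degrees of freedom, with 5 for therapists and 47 for controls, are 14.3. For v = 0.44:

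- SE² = 0.01238 + 0.00917, so SE = 0.147.
- Noncentrality = 0.5/0.147 = 3.41.
- Power from the noncentral t = 88.7%.

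A simulation of an unequal-variance t-test on therapist means against individual controls gives 88.0%. The stated 88% is therefore reproduced.

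**The same step for 16 weeks.** For v = 0.64:

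- SE² = 0.01800 + 0.01333, so SE = 0.177.
- Noncentrality = 0.5/0.177 = 2.82.
- Power = 74.9% (simulation 74.3%).

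**Dependence on the power method**, which the protocol does not state:

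| Method | SD 0.663 (average) | SD 0.80 (16 weeks) |
|---|---|---|
| Noncentral t, Satterthwaite df 14.3 | 88.7% | 74.9% |
| Normal, design effect 1.35 in both arms | 88.8% | 75.0% |
| t with 52 df | 91.7% | 79.2% |
| Normal approximation | 92.6% | 80.6% |

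Only the first two rows reproduce 88%. In every row the drop is 12 to 14 percentage points.

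**Sensitivity at 16 weeks (Satterthwaite).** ICC 0.02 gives 79.4% and ICC 0.10 gives 67.9%. At ICC 0.05, d = 0.60 is needed for 88% power.

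**The variance label.** Using 0.663 literally as a variance gives 73.4% (79.3% by the normal approximation). The 88% follows only if 0.663 is the SD, so the word in step 2 is wrong and the number used was right for an SD.

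**Inflation.** 96/0.74 = 129.7, so 130. This is correct.

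**The case against.** 1. **The model as listed matches the calculation.** Statistical methods {20a} lists no time or time-by-allocation term. Fitted literally, that model gives one allocation effect pooled over 16 and 28 weeks, which is what an SD of 0.663 powers. This is the strongest reply, and the time terms may simply be left to the analysis plan. It does not settle the matter: a single pooled effect is neither the 16-week endpoint in Outcomes {12} nor the per-time-point differences and p values promised in the same statistical section. On this reading the 88% is sound for the pooled effect, but the sections still disagree about what is primary.

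2. **The mixed model uses both follow-ups, so precision is recovered.** It is not recovered for a 16-week contrast. With complete data, a model with a separate effect at each visit has the single-visit, baseline-adjusted variance at 16 weeks. The 28-week data help only through participants seen at 28 but not 16 weeks, and that gain is small.

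3. **The 75% rests on an inferred method.** This is correct, and the figure should be quoted with that condition. The methods giving about 79% to 81% at 16 weeks, however, put the stated design at about 92% to 93%, not 88%.

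4. **More participants may be seen at 16 weeks than the 26% attrition implies.** The protocol does not tie the 26% to a visit. Assuming 10% to 20% loss at 16 weeks from 65 per arm, power is about 78% to 81%. The gap narrows but remains, and 48 completers per arm is the plan's own input.

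5. **Only wording changes.** Type I error, the estimate and its confidence interval are unaffected. That limits the consequence to how the trial's sensitivity is represented, but the stated power is still wrong for the declared endpoint.

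**Conclusion.** The concern holds. The 37 per arm and the 88% are both correctly calculated, but for the effect averaged over 16 and 28 weeks. For the declared 16-week endpoint, the protocol's own inputs give about 75% power at d = 0.5, some 13 to 14 points below the stated figure under the methods that reproduce it.

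This rests on two-sided 5% testing, 48 completers per arm at 16 weeks, an ICC of 0.05 applied to the adjusted variance, and a small-degrees-of-freedom correction. Relaxing the method or the attrition assumption one at a time raises the figure to at most about 81%. The SD/variance wording is a labelling error that does not affect this conclusion.

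**What to change.** Keep N = 130 and the 16-week endpoint. In Sample size {14}:

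- Redo both steps for one baseline and one follow-up (SD 0.80, variance 0.64). State the power as about 75% for d = 0.5, or the detectable effect as d of about 0.60 at 88% power.
- If the 88% is retained, label it as power for the average of the 16- and 28-week effects and give the 16-week figure beside it.
- State the power method, the degrees of freedom and the sidedness.
- Replace the variance wording in step 2 with an adjusted SD of 0.663 (variance 0.44), wherever that figure is kept.

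The primary model in Statistical methods {20a} should be reconciled with this by stating whether the primary contrast is at 16 weeks or pooled over both visits.

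The cost is a reworded paragraph and a less favourable stated power. No participants are added. For comparison, restoring 88% at 16 weeks with 6 therapists and ICC 0.05 would take about 13 completers per therapist: 2 × 6 × 13 = 156 completers, and 156/0.74 = 210.8, so about 211 recruited. Restating the power is therefore the practical course.
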